#### 1-month follow-up

The participants in both the intervention and control groups will be followed up via the mobile app at 1 month after the intervention, and a questionnaire will be conducted simultaneously. Their HPV vaccination status and HPV related knowledge will be assessed. Likewise, their personal motivation, intention and relevant behavioral skills regarding the injection of the HPV vaccine will also be examined. In addition, the intervention group will assess their satisfaction with the intervention.

#### 3-month follow-up

All measures from the 1-month questionnaire will be repeated in both groups, except for the satisfaction assessment of the intervention.

6-month follow-up: All measures from the 3-month questionnaire will be repeated in both groups, along with a reasons for vaccination refusal inquiry, if required.

### Measures

We will collect information from participants using a structured electronic questionnaire administered at four time points: at the study enrollment (baseline), 1 month after completing the digital education intervention (post-test), 3 months after the intervention and 6 months after the intervention (follow-up).

#### Outcome measures

Our primary outcomes of interest will be the difference between the intervention and the control group, which include: (1) knowledge, attitudes and beliefs about HPV, cervical cancer and the HPV vaccine; (2) intent to uptake the HPV vaccine; and (3) the reception of or an appointment for the first dose of the HPV vaccine.

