**Methods:**

This investigation is a multicenter, school-based, prospective, randomized, parallel group, double-blind, blank-controlled trial involving a 7-day education intervention with a further 6-month follow-up. We will enroll at least 3360 participants older than 18 years. The enrolled participants will be randomly divided into two groups (1:1 ratio). The intervention group will be offered a 7-day mobile health education, and participants in both groups will fill out 4 questionnaires at the baseline, 1 month, 3 months and 6 months after the intervention. The primary outcome is the difference in HPV vaccination or reservation for the HPV vaccine between the intervention and control groups. Secondary outcomes will include the comparison of (1) knowledge, attitudes, motivation, beliefs and behavioral skill about HPV and cervical cancer prevention, and (2) the willingness to uptake HPV vaccination.

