**Fig. 2 Fig2:**
[figure not shown]
Flow diagram of the study

We hypothesize that a mobile-based approach combining theory-based education and information about HPV, cervical cancer and the HPV vaccine may significantly improve HPV vaccination rates among participants.

Therefore, the primary objective of this study is to investigate the efficacy of a 7-day mobile-based intervention designed to increase HPV vaccination among Chinese female college students. The secondary objectives are to: (1) explore the impact of the intervention on knowledge, attitudes, and beliefs about HPV, cervical cancer and the HPV vaccine, (2) evaluate the short-term effect on uptake intention of the HPV vaccine, (3) determine the factors associated with the willingness of vaccination uptake and (4) identify the factors influencing HPV vaccination.

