### Sample size calculation

To date, no studies have investigated the effects of a mobile app-based intervention with Chinese female college students to improve the HPV vaccine uptake. For this reason, the anticipated effect size is largely based on findings derived from similar research literature in other countries. This study will apply a two-tail test with α = 0.05 and β = 0.20. Statistical power was originally calculated based on an absolute difference of 10% (20% of girls in the intervention group relative to 10% of girls in the control condition would initiate vaccination). The number of cases needed in each group of each sub-center is 119 as calculated by Statistical Analysis System (SAS) V.12. Allowing for a 20% rate of loss to follow-up, 240 cases are required in each group, and a total of 480 cases are required for each trial center. Consequently, this study requires a total of at least 3360 participants in 7 schools.

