### Statistical analysis

Since the study collects data through electronic questionnaires, there will be no formal data monitoring committee. Participants fill out the questionnaire and automatically upload it to a read-only database to ensure the authenticity of the data; however, all data will be reviewed by the research team at regular intervals throughout the study.

We will conduct all analysis using IBM SPSS Statistics 22.0, Version 22.0. Data will be checked for internal consistency and logic prior to further analysis. An intention-to-treat analysis will be performed. Descriptive statistics of all variables will be calculated, including means and standard deviations or frequencies as appropriate. We will assess the potential bias in enrollment and follow-up by comparing characteristics using a Wilcoxon Rank Sum, chi-squared, or Fisher Exact test as appropriate.

Proportions of qualitative variables will be compared between the intervention and control groups using chi-squared tests at baseline and repeated at 1 month, 3 months and 6 months after intervention. For each of these measures, the change in proportion from the baseline to these 3 point-ends will be tested within intervention groups using McNemar’s tests. Unadjusted odds of vaccine uptake and intent to vaccinate for the intervention participants versus the control participants will be calculated using a logistic regression model. Bivariable and multivariable logistic regression models will be used to determine the independent effect of the intervention. Results of logistic regression models will be expressed as odds ratios (ORs) and 95% confidence intervals (95% CIs). Measures of acceptability and satisfaction for intervention participants will be summarized using counts and sample proportions. All final statistical tests are two sided with α = 0.05.

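### The Outcome measures section makes knowledge and intent primary alongside vaccine uptake, which contradicts the abstract and objectives, and no primary time point is named

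*Protocol article*

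**What the plan says.** All references are to the protocol article.

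- **Abstract, Methods.** One primary outcome: "The primary outcome is the difference in HPV vaccination or reservation for the HPV vaccine between the intervention and control groups". The next sentence places the other domains lower: "Secondary outcomes will include the comparison of (1) knowledge, attitudes, motivation, beliefs and behavioral skill about HPV and cervical cancer prevention", followed by willingness to be vaccinated.
- **Background, objectives.** "the primary objective of this study is to investigate the efficacy of a 7-day mobile-based intervention designed to increase HPV vaccination". Knowledge, attitudes and beliefs form the first secondary objective. Intent is the second: "evaluate the short-term effect on uptake intention of the HPV vaccine".
- **Outcome measures.** "Our primary outcomes of interest will be the difference between the intervention and the control group, which include: (1) knowledge, attitudes and beliefs", and then "2) intent to uptake the HPV vaccine; and (3) the reception of or an appointment for the first dose of the HPV vaccine". All three items are introduced as primary.
- **Sample size calculation.** The planning rates are "20% of girls in the intervention group relative to 10% of girls in the control condition would initiate vaccination". No time point is attached to them.
- **Statistical analysis.** Proportions of qualitative variables are "compared between the intervention and control groups using chi-squared tests at baseline and repeated at 1 month, 3 months and 6 months after intervention". Every final test is two-sided at 0.05. Neither this section nor any other names a primary time point or says how several primary results combine into one conclusion.

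**The concern.** The section that defines the outcomes raises to primary status two domains that the abstract and the objectives call secondary. Both versions are printed, and no analysis plan could follow both.

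The choice decides what the trial may conclude. Its question is vaccine uptake, and the Background faults earlier Chinese studies for not assessing vaccination. The intervention is seven days of teaching compared with nothing, so a gain in knowledge or intent is a plausible result even if few more women are vaccinated. Under the Outcome measures wording that gain alone could be reported as a positive primary result. Even if only the uptake outcome were kept, it could still be claimed at whichever of the three follow-up surveys favoured it.

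**Working it through.** **1. Status of each domain, side by side**

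| Domain | Abstract | Objectives | Outcome measures |
|---|---|---|---|
| Knowledge, attitudes, beliefs | secondary | secondary | primary |
| Intent or willingness | secondary | secondary | primary |
| Vaccination, or booking a dose | primary | primary (vaccination) | primary |

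Two of the three rows conflict. Only the uptake row is primary everywhere.

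**2. Inputs for the error rate**

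- Primary domains: 3 (Outcome measures).
- Post-baseline test times: 3 (Statistical analysis).
- Level per test: 0.05, two-sided (Statistical analysis).
- Decision rule: none stated. *Assumption:* any one significant primary result counts as success.
- Correlation between test statistics: not given. *Assumption:* a common correlation ρ, varied from 0 to 0.9.

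The plan gives no familywise error figure, so there is none to reproduce.

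**3. Independent tests**

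Familywise error = 1 − (1 − 0.05)^k.

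- One outcome, one time (k = 1): 5%.
- Three outcomes at one time, or one outcome at three times (k = 3): 1 − 0.95³ = 14.3%.
- Three outcomes at three times (k = 9): 1 − 0.95⁹ = 37.0%.

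**4. Correlated tests**

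Familywise error = 1 − P(all |Zᵢ| < 1.96) for k normal statistics with common correlation ρ.

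| ρ | k = 3 | k = 9 |
|---|---|---|
| 0 | 14.3% | 37.0% |
| 0.3 | 13.6% | 32.6% |
| 0.5 | 12.5% | 26.9% |
| 0.7 | 10.9% | 20.2% |
| 0.9 | 8.4% | 12.4% |

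A simulation with separate correlations across times and across outcomes gives similar values for nine tests: 34.2% when both are 0.3, 22.7% when both are 0.7 and 13.7% when both are 0.9.

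**5. Does a single primary outcome cost power?**

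With 240 per group in each of 7 centers and 20% loss, 240 × 0.8 × 7 = 1,344 per arm remain. For 20% versus 10% at two-sided 0.05, power is above 99.9% trial-wide, ignoring any clustering. Going back to one primary outcome, tested once, needs no change to the stated sample size.

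**The case against.** The strongest reply is that the intended hierarchy is easy to recover. The abstract, the objectives, the Background and the sample size all point to uptake, and Outcome measures is the only outlier. Multiplicity rules and the primary time point are also often left to an analysis plan that is not shown. The second argument has force: absence of an adjustment would not be a finding by itself. It does not remove the contradiction, because an unseen plan would still have to depart from one of the two printed definitions.

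Three stronger readings are tempting, and the document does not support them.

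- **That the trial has a 37% false-positive rate.** This needs independent tests and a rule that any single success suffices, and the protocol states no such rule. If every test had to succeed, the rate would be at most 5%. Nine is also only a nominal count. The repeated chi-squared tests are stated for qualitative variables, the first domain rests on several multi-item scales (Baseline measures), and no between-group test of scale scores is described. Answers from the same women at three surveys will also be correlated.
- **That the sample size uses yet another outcome which excludes bookings.** The section speaks of initiating vaccination and is silent on appointments. It is unclear, but it does not say that they are excluded.
- **That counting an appointment is an error.** The abstract and Outcome measures both count a dose or a booking, and Follow-up measures likewise refers to receiving or ordering a dose. It is a declared composite. Teaching women how to obtain the vaccine is the intended mechanism and does not invalidate the endpoint. Nothing shows that an effect on bookings alone would be presented as an effect on doses.

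**Conclusion.** The concern holds as a contradiction over which outcomes are primary, made worse by the lack of a primary time point. It needs correcting, because it determines what may be claimed as the trial's main result. The contradiction is read directly from the text and needs no assumption.

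The size of the error inflation does rest on assumptions. Under an any-success rule it is at most about 14% for three outcomes at one time. For the nominal nine tests it is at most 37%, and roughly 12% to 33% for common correlations of 0.9 down to 0.3. These are familywise rates when the intervention has no effect on anything.

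**What to change.** 1. In Outcome measures, keep only receipt of, or an appointment for, the first dose as primary, assessed at the 6-month survey.
2. Move knowledge, attitudes, beliefs and intent to secondary, as in the abstract and objectives.
3. In Statistical analysis, make months 1 and 3 secondary time points.
4. Report first dose received separately from appointments, so that readers can see which component drives the result.
5. In Sample size calculation, say whether the 10% and 20% rates, stated for initiating vaccination, are meant for the composite or for doses received. If they are meant for the composite, give the reason; simply relabelling them would assert an assumption without checking it.

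The cost is mainly wording, with no change to the sample size. One check is needed. The article describes the 1-month and 3-month questionnaires as recording vaccination status and shows no separate appointment item, so the sponsor should confirm that the questionnaires distinguish a dose received from a dose booked.

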#### Baseline measures

We will collect participants’ HPV vaccination status, socio-demographic information (date of birth, nationality, religion, habitual residence, economic status, parental employment and marital status, and family or friends’ cancer history), health and sexual history. We will also record information about knowledge, cognition and beliefs related to HPV and HPV vaccination, motivations and intentions to uptake the HPV vaccine, decision-making, self-efficacy and objective skills regarding HPV vaccination. For background information, we will refer to the relevant part of several related studies conducted in China previously. The 11-item scale from Kahn JA and the HAVIQ (HPV Adolescent Vaccine Intervention Questionnaire) from Forster AS will be partly used to measure knowledge about HPV and HPV vaccination [30, 31]. For measuring cognition of HPV infection and prevention, we will use scales from Kim HW, Gerend MA and Guvenc G [32–34]. This will assess the perceived severity of HPV infection and the perceived benefits and barriers of HPV vaccination. Two scales from Ralph will be used to measure the perceived susceptibility of HPV infection [35]. The 5-item scale from Gerend MA will be adopted to test the influence of subjective norms [33]. For measuring decision-making for health protection, we will use the 3-item scale of Forster AS [31]. Self-efficacy for completing the 3-dose HPV vaccination will be tested using the 4-item scale of Gerend MA [33]. The self-administered 4-item scale developed by Fisher will also be used to measure the objective skills needed to initiate and complete HPV vaccination [26]. Finally, intent to receive the HPV vaccine will be measured according to the answer to the question: “Willingness to take the HPV vaccine in the next 6 months”.

#### Post-test measures

At the 1-month follow-up, we will administer a post-test survey of the same information collected at the baseline, except for background information. Furthermore, we will measure participant satisfaction with the mobile app-based education to provide information for improving similar studies in the future.

#### Follow-up measures

At the 3-month follow-up, excluding the satisfaction assessment of the intervention, we will measure the same items collected during the 1-month follow-up test. For participants not receiving or ordering a dose of the HPV vaccine during the trial period, we will ask for the reasons for vaccine hesitation or refusal at the 6-month follow-up survey.

### Sample size calculation

To date, no studies have investigated the effects of a mobile app-based intervention with Chinese female college students to improve the HPV vaccine uptake. For this reason, the anticipated effect size is largely based on findings derived from similar research literature in other countries. This study will apply a two-tail test with α = 0.05 and β = 0.20. Statistical power was originally calculated based on an absolute difference of 10% (20% of girls in the intervention group relative to 10% of girls in the control condition would initiate vaccination). The number of cases needed in each group of each sub-center is 119 as calculated by Statistical Analysis System (SAS) V.12. Allowing for a 20% rate of loss to follow-up, 240 cases are required in each group, and a total of 480 cases are required for each trial center. Consequently, this study requires a total of at least 3360 participants in 7 schools.

### Statistical analysis

Since the study collects data through electronic questionnaires, there will be no formal data monitoring committee. Participants fill out the questionnaire and automatically upload it to a read-only database to ensure the authenticity of the data; however, all data will be reviewed by the research team at regular intervals throughout the study.

We will conduct all analysis using IBM SPSS Statistics 22.0, Version 22.0. Data will be checked for internal consistency and logic prior to further analysis. An intention-to-treat analysis will be performed. Descriptive statistics of all variables will be calculated, including means and standard deviations or frequencies as appropriate. We will assess the potential bias in enrollment and follow-up by comparing characteristics using a Wilcoxon Rank Sum, chi-squared, or Fisher Exact test as appropriate.

Proportions of qualitative variables will be compared between the intervention and control groups using chi-squared tests at baseline and repeated at 1 month, 3 months and 6 months after intervention. For each of these measures, the change in proportion from the baseline to these 3 point-ends will be tested within intervention groups using McNemar’s tests. Unadjusted odds of vaccine uptake and intent to vaccinate for the intervention participants versus the control participants will be calculated using a logistic regression model. Bivariable and multivariable logistic regression models will be used to determine the independent effect of the intervention. Results of logistic regression models will be expressed as odds ratios (ORs) and 95% confidence intervals (95% CIs). Measures of acceptability and satisfaction for intervention participants will be summarized using counts and sample proportions. All final statistical tests are two sided with α = 0.05.

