### Sampling and randomization

The study process consists of the following four phases:

Phase 1: Confirm the stratified sampling framework by geographical territories of China.

The stratified sampling of the 31 provinces/municipalities/autonomous regions in China is conducted from seven geographical territories, namely East China, South China, Central China, North China, Northwest China, Southwest China and Northeast China.

Phase 2: Convenient sampling to determine the cities and universities to be included within the geographic territories in Phase 1.

We select a representative city in each of the seven geographical territories using the convenient sampling method. A total of 7 cities (Jinan of Shandong Province, Guangzhou of Guangdong Province, Zhengzhou of Henan Province, Beijing, Urumqi of Xinjiang Uygur Autonomous Region, Chengdu of Sichuan Province, Dalian of Liaoning Province) were finally decided to be the study sites. In each representative city, a comprehensive university is selected. A total of 7 universities (Shandong University, Zhongshan University, Zhengzhou University, Capital Normal University, Xinjiang University, Sichuan University, Dalian University of Technology) are finally confirmed as research centers for this study.

Phase 3: Cluster sampling in each of the seven research centers.

After satisfying the inclusion criteria, at least 240 university students will be selected by class from the literature and science majors (excluding medical majors) respectively, and a total of 480 samples will be composed at each of the seven centers. This selection will result in a total of at least 3360 participants across 7 schools.

Phase 4: Randomization and allocation in each center.

After the baseline survey, all identified participants will be randomly assigned to the intervention group or control group in a 1:1 ratio, and each group at each center will have 240 participants. Randomization will be stratified with regards to majors, resulting in two separate categories of literature and science majors. The random sequence will be generated using SAS V.12. (SAS Institute) software. Furthermore, randomization will be conducted by personnel not involved in the trial at each of the seven universities.

After randomization, the researcher who assigns participants to the intervention will provide information about the mobile-based education. This researcher will no longer be blinded from this point.

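### The specified between-arm comparisons of intent and uptake leave out baseline intent, while baseline differences between randomised arms get an uninformative significance test

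*Protocol article*

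**What the plan says.** All references are to the protocol article.

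- **Order of events.** Sampling and randomization: "After the baseline survey, all identified participants will be randomly assigned to the intervention group or control group in a 1:1 ratio". Allocation is stratified by major (literature or science) at each centre. Intent is not a stratifier.
- **Between-arm tests.** Statistical analysis: "Proportions of qualitative variables will be compared between the intervention and control groups using chi-squared tests at baseline and repeated at 1 month", and again at 3 and 6 months.
- **Effect models.** Same section: "Unadjusted odds of vaccine uptake and intent to vaccinate for the intervention participants versus the control participants will be calculated using a logistic regression model". It then adds: "Bivariable and multivariable logistic regression models will be used to determine the independent effect of the intervention". No covariates are named.
- **Other uses of baseline values.** Same section: "the change in proportion from the baseline to these 3 point-ends will be tested within intervention groups using McNemar’s tests", and "We will assess the potential bias in enrollment and follow-up by comparing characteristics using a Wilcoxon Rank Sum, chi-squared, or Fisher Exact test as appropriate".
- **Baseline intent.** Baseline measures: "intent to receive the HPV vaccine will be measured according to the answer to the question", which asks about willingness to be vaccinated in the next six months. Post-test measures and Follow-up measures repeat the non-background items at later waves. Outcome measures lists intent among the primary outcomes.

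**The concern.** Two things look wrong.

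First, the baseline test has a null hypothesis that is true by design. A significant result is a false alarm. A non-significant result does not remove whatever imbalance is present.

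Second, the answer to the same question before the intervention is likely to be a strong predictor of intent at follow-up. The comparisons that are spelled out do not use it. The only tests of change from baseline are within groups, and these do not compare the arms.

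The article's own Discussion shows how this layout can be read. It describes an earlier school-based trial as a significant improvement because vaccination rose from 52.5% to 59% after the intervention while the control group stayed at 60.9%. On those figures the control group was still the higher one afterwards, so the handling of baseline decides what is concluded.

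At stake are power for intent, which costs nothing to gain, and a baseline table that may report chance differences as findings.

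**Working it through.** The plan attaches no figure to this point, so there is none to reproduce. The 119 per group in the sample size section is not an input here.

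**Inputs from the article.** 240 per group at each of 7 centres, so 7 × 240 = 1680 per arm. Loss of 20%, so 0.8 × 240 = 192 per group per centre and 0.8 × 1680 = 1344 per arm. Uptake 10% versus 20%. Two-sided α = 0.05.

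**Assumptions.** Baseline willingness 50%. Follow-up intent 50% versus 57% with 700 per arm. Odds ratio between baseline intent and outcome of 2, 5 or 10. The article gives none of these.

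**1. Baseline tests.** With k tests at 0.05, the expected number of false alarms is 0.05k. If the tests were independent, the chance of at least one is 1 − 0.95^k.

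| k | Expected | Chance of at least one |
|---|---|---|
| 5 | 0.25 | 23% |
| 10 | 0.5 | 40% |
| 20 | 1 | 64% |

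The article does not state k. Items within one scale are correlated, so the last column is only a guide.

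**2. Chance imbalance in intent.** The SD of the baseline difference is √(2 × 0.25/1680) = 0.017. The 95% range is ±1.96 × 0.017, about ±3.4 points. The standard error of an unadjusted comparison already allows for such chance variation.

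**3. Where baseline values enter.**

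| Analysis | Compares arms? | Uses baseline intent? |
|---|---|---|
| Chi-squared at baseline | Yes | As the thing tested |
| Chi-squared at 1, 3, 6 months | Yes | No |
| Unadjusted logistic model | Yes | No |
| McNemar | No | Yes, as change within a group |
| Enrolment and follow-up bias check | No effect estimate | Not stated |
| Multivariable logistic model | Yes | Not stated |

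**4. Gain from adjustment.** Logistic models with arm alone, and with arm plus baseline intent, were fitted to the same 600 simulated data sets per row.

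| Outcome | Odds ratio with baseline intent | Power, unadjusted | Power, adjusted | Gain (points) |
|---|---|---|---|---|
| Intent, 50% vs 57%, 700 per arm | 2 | 0.763 | 0.770 | 0.7 |
| | 5 | 0.768 | 0.835 | 6.7 |
| | 10 | 0.750 | 0.875 | 12.5 |
| Uptake, 10% vs 20%, 192 per arm | 2 | 0.792 | 0.792 | 0 |
| | 5 | 0.805 | 0.830 | 2.5 |
| | 10 | 0.782 | 0.815 | 3.3 |

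The simulation error of a single power figure is about √(0.77 × 0.23/600) = 0.017. The simulation ignores centre and class.

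**5. Transfer to the full trial.**

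- Intent, simulated case: 0.07/√((0.25 + 0.2451)/700) = 2.63.
- Intent, 50% versus 55% with 1344 per arm: 0.05/√((0.25 + 0.2475)/1344) = 2.60. The simulated case therefore stands for a difference of about 5 points at the planned size.
- Intent, 50% versus 57% with 1344 per arm: 0.07/√(0.4951/1344) = 3.65. Unadjusted power is then about 95%, which leaves less to gain.
- Uptake, 10% versus 20% with 1344 per arm: 0.10/√((0.16 + 0.09)/1344) = 7.3. Power is already close to 100%, so the uptake gain in step 4 applies to a single centre.

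**The case against.** The strongest reply is that the unadjusted analysis is sound. Under randomisation its type I error and confidence interval already reflect chance imbalance, and the arms are compared directly at every follow-up. A stray significant result in the baseline table changes no effect estimate, because the plan does not make adjustment depend on it. All of this stands, and it limits the point to efficiency and reporting.

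Several stronger readings are tempting, and the article does not support them:

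- **Baseline values are used only in the between-arm chi-squared tests.** They also enter the McNemar tests, and a comparison of characteristics is planned to assess enrolment and follow-up bias.
- **Baseline intent never enters the effect comparisons.** A multivariable logistic model is planned with unnamed covariates, so baseline intent is neither included nor excluded. A covariate list is commonly left to the full protocol or SAP, which are not shown, and its absence is no fault here.
- **The effect model will contain follow-up knowledge, motivation or skill scores.** Nothing in the text proposes this. It would be an inference from silence.
- **Adjustment cuts the variance by the squared correlation.** That is a linear-model result. In a logistic model the standard error of the log odds ratio generally rises, while the conditional odds ratio moves away from 1. Power can improve, so the gain belongs on the power scale.

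**Conclusion.** The point holds as one of efficiency and reporting. It is not one of bias or invalidity. The baseline significance tests between randomised arms are uninformative. The between-arm comparisons that the article spells out forgo baseline intent, and the multivariable step does not commit to it.

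For intent, the simulated gain is about 1 to 13 points of power where unadjusted power is about 75% to 77%. It is smaller where the trial is already well powered. For uptake, the gain is 0 to about 3 points at single-centre size and practically nil when centres are pooled at the planning rates.

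These sizes rest on the assumed 50% baseline willingness, the assumed effect on intent, and above all the assumed association between baseline intent and outcome. Removing the baseline tests is good practice but alters no effect estimate.

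**What to change.** 1. Make the main comparison of intent at each wave a logistic regression of outcome on arm, with baseline intent as a covariate fixed in advance and kept whatever the baseline comparison shows. Do the same for uptake, where the gain is small.
2. State that the effect model uses only covariates measured at baseline.
3. Keep the unadjusted odds ratio as supportive, and note that the adjusted odds ratio is conditional on baseline intent, so the two are not expected to agree exactly.
4. Replace the between-arm chi-squared tests at baseline with a description by arm. The plan already provides descriptive statistics for all variables.

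The cost is a change of wording in the analysis section, or in the SAP if one exists. Baseline intent is already collected, so neither the questionnaire nor the sample size changes.
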